### Interventions

#### Physical exercise programs

First, the common aspects between the two exercise groups are going to be mentioned, to explain afterwards the peculiarities of each physical exercise program. The programs of both experimental groups, PEG and HRVG, will last 14 weeks, and patients will train three times per week. All sessions will be supervised and remote. So that, each patient will connect with the physical exercise professional and with the other 4 participants by videocall. Moreover, the practitioner will monitor their heart rate in real-time because each patient will be given a MyZone heart rate (HR) control and platform access to MZ-Remote. In this way the professional will be able to adjust their workout intensity according to their HR, in the cardiovascular exercises and the weightlifting load in the resistance exercises; and to control and correct, participants’ posture and technique. Moreover, these measures will be determinant to asses participants’ exercise adherence. During the sessions, participants will be able to see their HR and HR of the rest of their training group. In addition, to promote social interaction an extra link will be given to those patients which want to see each other while practicing exercise. The necessary material to perform the exercise programs will be given to each participant in the before-intervention evaluation. This training kit will include a barbell of 2 kg, 2 weight discs of 5 kg, 2 weight discs of 2.5 kg, 2 weight discs of 1.25 kg and a Myzone's MZ-3 Belt chest strap.

Each session will last approximately 60 min and will include a warm-up, a main part composed of cardiovascular resistance exercises and a cooldown. The warm-up, lasting from 5 to 10 min, will include upper, lower body and truck mobility, and core muscular activation. The cooldown part will last about 5 min and will combine stretching of the muscles involved during the corresponding session. Moreover, during the stretches, breathing feedback will be given to fully relax and enhance elongation during the exhalation phase.

As for the main part of the sessions, lasting from 45 to 50 min approximately, the training schedule will be divided into three mesocycles. The first, with a duration of 4 weeks, will be focused on neuromuscular adaptation, learning exercise techniques and improving participants' aerobic capacity and HR self-control. In this regard, the exercises proposed in the period will be of low complexity and will be performed with the lowest program intensity. In the 5th week will begin the second mesocycle until week 10th when the intensity will increase progressively including exercises with greater technical complexity. In the last mesocycle from weeks 11th to 16th participants will experiment with the highest level of technical complexity and intensity archiving the highest weight load and cardiovascular intensity. In this way, the sessions, and their progression, will be designed according to the principles of training to achieve the greatest possible adaptations [49]. Concretely, during the first mesocycle, the participants will alternate two training circuits and during the second and third mesocycle patients will combine 3 different circuits, one each training day of the week. Part of the exercises has a cardiovascular component through intervallic training. These exercises will be combined with resistance training by performing them either at the beginning of the circuit, or between the strength exercises, or at the end of the strength circuit.

The cardiovascular component of the exercise program will be performed with different exercises such as: walking with knees up, jogging in place, skipping, sideways running by changing direction, jumping jacks, etc. The duration of the cardiovascular and its intervallic duration will vary in each mesocycle. In the first one, participants will perform 2 sets composed of 4 repetitions of 1 min with 45 s of rest between intervals and 2 min between sets. In the second and third mesocycles, the cardiovascular sets will be conducted between each resistance exercise. In this way, each circuit repetition will include 5 sets composed of 3 intervals of 30 s with 10 s of resting between repetitions in circuits 3, 4, 6 and 7. Whereas in circuits 5 and 8, which will be carried out on the third day of the training week of the second and third mesocycle, the intervals will be developed at the end of all the resistance exercises. Furthermore, every 6 weeks, on the third training day, the cardiovascular interval part will be done with dancing choreographies with the songs chosen by participants. Furthermore, every 5 weeks, on the third training day, the cardiovascular interval part will be done inside dancing choreographies with songs chosen by participants.

Regarding the resistance exercise of the training program, exercises will combine lower body strength with a predominance of both knees (e.g. squat or stride) and hip (e.g. deadlift or hip thrust) and upper body strength exercises of pushing (e.g. chest press, shoulder press or arm-triceps extension) and gripping (e.g. rowing or biceps curl). As mentioned, participants will progress in the complexity of the exercises, for example, from a squat starting from a chair to a barbell squat, or from a gluteal bridge to hip thrust. Table 1 shows a programming example that can serve as a reference for a better understanding of what the intervention will entail.

**Table 1 Tab1:** Example of the main part of the physical exercise program

1st to 4 th week of exercise	
Circuit 1	Circuit 2
Walking rising knees (4 × 1 min) (2 sets) 1. Chair squat 2. Biceps curl 3. Lunge in place 4. Incline raw	Jog in place (4 × 1 min) (2 sets) 1. Hip trust 2. Triceps elbow extension 3. Chair squat 4. Chest press
Participants will repeat each circuit 4 times. Resistance exercise: 12 to 14 repetitions (HRVG) and 10 to 12 repetitions (PEG) in each circuit set. Rest: 20 s rest between exercises and 2 min between each of the laps of the circuit.	

5th to 10 th week of exercise			11th to 16th week of exercise		
Circuit 3	Circuit 4	Circuit 5	Circuit 6	Circuit 6	Circuit 7
1. Skipping 2. Biceps curl 3. Skipping 4. Triceps elbow extension 5. Skipping 6. Chest press 7. Skipping 8. Shoulder press	1. Jogging 2. Squat 3. Jogging 4. Dead lift 5. Jogging 6. Lunge 7. Jogging 8. Hip trust	1. Squat 2. Chest press 3. Hip trust 4. Incline raw 5. Lunge 6. Shoulder press Cardiovascular exercise*	1. Sideways running 2. Chest press 3. Sideways running 4. Shoulder press 5. Sideways 6. Biceps curl 7. Sideways running 8. Incline raw	1. Jumping jacks 2. Lunge 3. Jumping jacks 4. Dead lift 5. Jumping jacks 6. Squat 7. Jumping jacks 8. Hip trust	1. Squat 2. Shoulder press 3. Dead lift 4. Incline raw 5. Lunge 6. Chest press Cardiovascular exercise*
Participants will repeat each circuit 2 times Resistance exercises: 2 sets of 10–12 repetitions (HRVG) and 8–10 repetitions (PEG) Rest: 1 min rest between sets and 2 min between circuit repetition			Cardiovascular exercise: 3 sets os 30 s-interval + 10 s rest (circuits 3, 4, 6 and 7). 2 sets of 6 × 30 s-intervals repetitions + 10 s rest (circuits 5 and 8) * Dance activities once every 4 weeks		

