**Methods:**

For this purpose, a 16-week intervention will be carried out with 90 breast cancer patients distributed in 3 groups (a control group, a moderate to high-intensity preplanned exercise group and a high-intensity exercise group guided by HRV). Both physical exercise interventions will be developed remotely and supervised including strength and cardiovascular exercises. Physiological variables, such as cardiotoxicity, biomarkers, lipid profile, glucose, heart rate and blood pressure; physical measures like cardiorespiratory capacity, strength, flexibility, agility, balance and body composition; and psychosocial variables, as health-related quality of life, fatigue, functionality, self-esteem, movement fear, physical exercise level, anxiety and depression will be measure before, after the intervention and 3 and 6 months follow up.

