## Methods/design

### Study design

The research will be conducted following the Helsinki declaration [43] and the American Society of Clinical Oncology policy statement [44]. Patients will be randomly assigned to three groups where two of them will participate in a physical exercise intervention and the left group will continue with usual care for 16 weeks (see Fig. 1). Moreover, the study methods described below follow the Standard Protocol Items Recommendations for Interventional Trials (SPIRIT) of 2013 [45] (SPIRT schedule and checklist are shown in the Additional file 1). After the positive response from the ethics committees, the trial was registered at ClinicalTrials.gov, recognized by the World Health Organization and the International Committee of Medical Journal Editors, under the identification number of NCT05040867.

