##### High-intensity remote physical exercise program guided daily by HRV

Although all participants will daily measure their HRV, only in this intervention group each day's results will influence their exercise intensity. From the outcomes reported with smartphone photoplethysmography, explained the measurement process in the outcomes part, the root means squared differences of successive RR intervals (rMSSD) will be chosen as a reflection of vagal activity to prescribe the workout intensity [50]. In this regard, the natural logarithm of rMSSD will be calculated to make parametric statistical comparisons assuming a normal distribution. For establishing the training intensity and load, a 7-day rolling average measure (LrRMSSD7day-roll-avg) will be utilized. Subsequently, the scoring obtained will be contrasted in the smallest worthwhile change (SWC) to analyze if the daily result is inside SWC upper and lower limits, calculated as LnrMSSD reference week mean ± 0.5 × SD [51, 52]. The reference week of the first 4 training weeks will take the limits created in the baseline week, and in the rest of the program, an updated measure will be carried out every 4 weeks with the SWC for the past 4 weeks, because of the influence of exercise in participants cardiac autonomic modulation [53].

In this regard, when the daily LnrMSSD fell inside the limits created by the SWC patients will perform high-intensity training characterized by a cardiovascular intensity from 80 to 95% of their reserve HR (increasing a 5% every four weeks) and a weighting load from 70 to 85% of their RM (increasing the load 5% ever mesocycle, four weeks). Whereas if any day patients’ scoring fell out of the SWC, they will train at the same intensity as the PEG (Fig. 2).

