
Finally, the strength-power will be measured by employing a countermovement jump test (CMJ) and from squat (SJ) to evaluate the explosiveness of the patient, as has been done in previous studies on patients with breast cancer [88]. it was decided to eliminate the assessment of hip trust and triceps barbell strength, included in the clinical registration because performing all the tests would take too long for the patients.

Vertical applied force. The force-power will be measured utilizing a CMJ and from SJ as a reflection of the application of force in the unit of time, inter and intramuscular coordination and the use of the elastic energy of those actions in which the stretch–shortening cycle of the lower limbs predominates, which is present in the majority of actions in daily life, as has been carried out in previous studies in patients with breast cancer [88]. In the evaluations after the intervention, those patients in whom it is possible to evaluate the jump with progressive loads, the vertical force–velocity profile will be performed, which will give us information on how the subject is currently producing power and how it should (based on their characteristics) in order to be able to evaluate the explosiveness of the patients [89]. To obtain it, together with the SJ and CMJ jumps without load, the patients will perform 2–3 more attempts with progressive loads, determining the increase in load according to the height of the jump without weight [90]. In addition, for the corresponding calculations, two body measurements will be taken to determine the push-off distance (pod). For the evaluation of the different variables indicated, different technologies will be used such as the Chronojump’s contact platform and the recording with an IOS camera of 240 f.p.s of each of the jumps for subsequent analysis with the validated application of My Jump [91] and Kinovea [92].

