Relatedly, the second aspect to highlight is the novelty of the exercise interventions compared to ones perform so far analyzing cardiotoxicity variables. To date, from our perspective, is the first study that will apply high and moderate to high-intensity cardiovascular and resistance training in breast cancer patients to analyze the cardiotoxicity effects, among others. Furthermore, except for one study protocol recently published [128] and a few studies in rats [129, 130], it would be also one of the first of including resistance training with so high weight and volume loads. Moreover, regarding exercise timing, the exercise programs focused on the improvement of cardiotoxicity variables such as LVEF, GLS, or troponin, most of the studies are carried out during breast cancer patients’ treatments [131] and not after them as our study will perform. However, cardiac abnormalities in breast cancer patients may appear within the first year after the end of chemotherapy, in case of early cardiotoxicity, or after several years following the completion of treatment (median of 7 years) [4]. Accordingly, to improve patients' cardiorespiratory fitness, troponin and GLS values and maintain the levels reached by acquiring physical exercise habits, in the current study patients have recently finished chemotherapy and radiotherapy to prevent the potential early and late cardiotoxicity. We will try to teach patients how to train during the 16 weeks of the exercise programs and to generate positive and self-determination experiences through exercise [132]. So that, we will promote exercise adherence to continue exercising even after its end knowing their cardiovascular and resistance levels at the end of the programs. Moreover, maybe if exercise programs are developed uniquely during chemotherapy or before it, patients can associate exercise to unpleasant cancer treatments or phases being unlikely to maintain exercising after treatments.

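### The stated exercise dose is internally inconsistent: 14 versus 16 weeks, four-week steps versus 4/6/6-week mesocycles, two lifts loaded by %RM without an RM test, and a 19.5 kg kit that caps the final load for stronger lifts

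*Protocol article*

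**What the plan says.** **Length.** Physical exercise programs states: "The programs of both experimental groups, PEG and HRVG, will last 14 weeks", with three sessions per week. The abstract says "a 16-week intervention will be carried out with 90 breast cancer patients". Study design says that "the left group will continue with usual care for 16 weeks". The Discussion speaks of teaching patients to train "during the 16 weeks of the exercise programs". The schedule in Physical exercise programs has a first mesocycle of 4 weeks, a second from week 5 to week 10, and a third described thus: "In the last mesocycle from weeks 11th to 16th participants will experiment with the highest level of technical complexity". Table 1 uses the same blocks and labels the last one as weeks of exercise.

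**Intensity.** Loads are set as a percentage of RM in both arms. The pre-planned arm (PEG) goes from 55% to 70% RM and from 65% to 80% of reserve heart rate. On days within its HRV limits, HRVG trains at 80% to 95% of reserve heart rate, rising 5% every four weeks, and at "a weighting load from 70 to 85% of their RM (increasing the load 5% ever mesocycle, four weeks".

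**RM tests.** In the strength measurement section "it was decided to eliminate the assessment of hip trust and triceps barbell strength". Hip thrust stays in Table 1 in all three phases, and triceps extension stays in circuits 2 and 3.

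**Kit.** Each participant trains at home with "a barbell of 2 kg, 2 weight discs of 5 kg, 2 weight discs of 2.5 kg, 2 weight discs of 1.25 kg".

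**The concern.** These are positive statements that cannot all hold; they are not gaps left by condensing a protocol into an article. Three things depend on them.

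- **Dose and visit timing.** The post-intervention visit and the 3- and 6-month follow-ups are all counted from the end of the intervention. Usual care is set at 16 weeks, so a 14-week programme could place the exercise and control assessments at different times. The Background says that programmes aimed at cardiotoxicity seem to need at least 36 sessions, and the attendance needed to reach 36 depends on the length.
- **The HRVG prescription.** The step rule defines what HRVG receives beyond PEG. If staff can read it in two ways, the HRVG-PEG contrast is not fixed.
- **Delivered load.** The Sample size section bases its calculation on intensity differences between groups. If the kit limits load for some lifts, the load contrast achieved for those lifts may be smaller than planned, and a null HRVG-PEG result on strength would be hard to interpret.

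**Working it through.** **1. Length and sessions.** Mesocycles: 4 + (10 − 5 + 1) + (16 − 11 + 1) = 4 + 6 + 6 = 16 weeks. The stated 14 weeks does not follow from the schedule.
- 14 × 3 = 42 sessions; 16 × 3 = 48 sessions. The difference is 6, and 6/48 = 12.5%.
- Attendance needed for 36 sessions: 36/42 = 86%, or 36/48 = 75%.

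**2. Step timing for HRVG.** Going from 70% to 85% RM in 5-point steps takes four levels (70, 75, 80, 85). Three mesocycles give three levels.

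| Weeks | Mesocycle | %RM, four-week steps | %RM, one step per mesocycle | % reserve HR, four-week steps |
|---|---|---|---|---|
| 1–4 | 1 | 70 | 70 | 80 |
| 5–8 | 2 | 75 | 75 | 85 |
| 9–10 | 2 | 80 | 75 | 90 |
| 11–12 | 3 | 80 | 80 | 90 |
| 13–16 | 3 | 85 | 80 | 95 |

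The two load readings differ in weeks 9–10 and 13–16, which is 6 of 16 weeks. With four-week steps the top level lasts four weeks in a 16-week programme and two weeks (13–14) in a 14-week programme. With one step per mesocycle the load ends at 80% RM, below the section's own 85%.

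**3. Lifts trained against lifts tested.** RM tests remain for squat, deadlift, lunge, chest press, shoulder press, bent-over row and biceps curl. Hip thrust and triceps extension are trained without one.

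**4. Kit ceiling.** Kit maximum = 2 + 2×5 + 2×2.5 + 2×1.25 = 19.5 kg. The highest RM at which a target p is reachable is 19.5/p:
- 85%: 19.5/0.85 = 22.9 kg
- 70%: 19.5/0.70 = 27.9 kg
- 55%: 19.5/0.55 = 35.5 kg

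The protocol gives no RM values. The RMs below are assumed for illustration. Loads are in kg, capped at 19.5 where the target exceeds it.

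| Assumed RM | PEG start (55%) | HRVG start (70%) | PEG end (70%) | HRVG end (85%) | Difference at end |
|---|---|---|---|---|---|
| 20 | 11.0 | 14.0 | 14.0 | 17.0 | 3.0 (as planned) |
| 25 | 13.75 | 17.5 | 17.5 | 19.5 (target 21.25) | 2.0 (planned 3.75) |
| 30 | 16.5 | 19.5 (target 21.0) | 19.5 (target 21.0) | 19.5 (target 25.5) | 0 (planned 4.5) |
| 40 | 19.5 (target 22.0) | 19.5 (target 28.0) | 19.5 (target 28.0) | 19.5 (target 34.0) | 0 (planned 6.0) |

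Up to 22.9 kg the planned loads stay under the cap. From 22.9 to 27.9 kg the final contrast narrows. From 27.9 kg it is zero at the end, and from 35.5 kg it is zero from the start.

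**The case against.** **The length conflict is one sentence against five other places, and it affects PEG and HRVG alike.** This stands. A reader might infer that it separates the two exercise arms, and it does not. It leaves total dose and visit timing unclear in both. Reading it as 14 training weeks plus 2 assessment weeks fails, because Table 1 counts weeks 11 to 16 as exercise and the Discussion gives 16 weeks to the exercise programmes themselves.

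**Four-week steps fit a 16-week programme.** They reach 85% RM and 95% of reserve heart rate, and the top level falls within the last mesocycle, which is described as the most intense. The heart-rate step and the update of the HRV limits also run every four weeks. All this stands, so one should not infer that HRVG is planned to end at 80% RM. What remains is a rule that equates a mesocycle with four weeks when two of the three last six.

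**The kit may suffice.** For lifts with an RM up to 22.9 kg the whole range from 55% to 85% stays under the cap, and nothing in the protocol shows how many lifts exceed it. This stands. A reader might infer that %RM loading cannot be delivered at all, or that the resistance contrast disappears; neither is supported. Table 1 also gives the arms different repetitions (12–14 against 10–12 in weeks 1–4, later 10–12 against 8–10), and the heart-rate targets do not depend on the kit.

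**The RM-test gap concerns two lifts, and Table 1 is labelled an example.** It does concern only two. However, the running text also names both kinds of exercise, and the %RM rule is stated without exception.

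**Sessions are already monitored.** Heart rate is followed in real time, the professional adjusts the load, and these measures serve to assess adherence. That makes the remedy cheap but does not remove the contradictions.

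**Conclusion.** The point holds as a set of inconsistencies in the stated dose.

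- **Without any assumption:** the length is 14 or 16 weeks (42 or 48 sessions). The step rule and the mesocycle schedule disagree on load in 6 of 16 weeks, and one step per mesocycle misses the stated 85% endpoint. Two trained lifts have no RM test behind their %RM load.
- **Conditional on RM:** if the listed kit is all the external load available, the final load contrast is lost for lifts with an RM of 27.9 kg or more, and the load contrast is absent throughout from 35.5 kg. The repetition and heart-rate contrasts remain. The share of participants and lifts affected is unknown: the protocol describes the RM tests as planned and reports no results.

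Which length, step or load is intended cannot be decided from the protocol and is not judged here.

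**What to change.** 1. Reconcile the abstract, Study design, Physical exercise programs (both the opening statement and the mesocycle schedule), Table 1 and the Discussion to one programme length. Tie the post-intervention visit to it in all three arms, so that control and exercise assessments fall at the same time.
2. Reconcile the mesocycle schedule with the HRVG section: state whether load steps follow four-week blocks or mesocycles, and make the steps agree with the stated endpoint.
3. Reconcile the %RM wording for both arms with the kit mass and with the two untested lifts. Once RM tests are available, tabulate by lift how many participants exceed each ceiling.
4. Record achieved load (as a percentage of tested RM where a test exists) and heart rate at each session, and report the delivered contrast by arm.

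No dose, load or duration is proposed; those are for the investigators to settle. The cost is protocol wording, a session log that builds on monitoring already planned, and possibly a change to the kit.

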##### Pre-planned remote moderate to high-intensity physical exercise program

The current exercise group will perform exercise following the recommendations of several and important literature such as the American College of Sports Medicine guidelines carrying the exercise with an intensity going from moderate to high intensity. Concretely in the cardiovascular exercise, the participant will start with an intensity of 65% of their reserve HR, in the first mesocycle; and will end with an intensity of 80% of their reserve HR. In the resistance exercise, they will commence lifting weights corresponding to their 55% RM and finish in the last mesocycle lifting loads matching their 70% RM.

